## Assignment of interventions: blinding

### Who will be blinded {17a}

This is a patient-assessor-blinded study. To ensure that participants are blind, they will be treated in an isolated space and be required to wear blindfolds. Only the acupuncturist who performs the treatment will know the group assignment at the time of treatment. Gastroenterologists, data analysts, and statisticians will remain blinded.

### Procedure for unblinding if needed {17b}

Unmasking is not needed.

## Data collection and management

### Plans for assessment and collection of outcomes {18a}

We will record the evaluation results in the CRFs in a timely fashion.

### Plans to promote participant retention and complete follow-up {18b}

Patients will come to the hospital 1 week after gastroscopy to complete the final questionnaires. We will follow up and debrief patients at this time point. At the end, patients will receive a transportation subsidy.

### Data management {19}

Patient characteristics will be recorded in the CRFs and stored in the researcher’s office. The clinical trial management platform ResMan will be used to manage the raw data. The raw data will be collected by assessors who are blinded to the group assignment and repeated input methods will be used to ensure that the entered data is correct. Before the platform is officially launched, it will be tested and the users will be trained. After the platform is officially launched, the database will be locked with a password, which will only be known by relevant personnel. The clinical director will oversee the work of the clinical trial center at least once a month.

### Confidentiality {27}

All the documents and materials related to this will be kept strictly confidential. Only once the trial is finished will the principal investigator distribute the data to the third parties. We will protect the privacy of participants’ personal medical information as required by law. The staff in this study is also bound by this agreement.

### Plans for collection, laboratory evaluation, and storage of biological specimens for genetic or molecular analysis in this trial/future use {33}

Not applicable. This trial does not have biological specimens.

## Statistical methods

### Statistical methods for primary and secondary outcomes {20a}

The independent statistician is responsible for the statistical analysis with spss24.0 software. Patient data that falls off will not be included in the analysis. In the statistical analysis, measurement data between the two groups will be analyzed with the *t*-test and rank-sum test, while categorical data will be analyzed with *χ*^2^ test. Data will be recorded as mean ± standard deviation or median (first quartile, third quartile). The significance level used for statistical analysis will be two-sided with confidence intervals at the 95% level.

### Interim analyses {21b}

Not applicable.

### Methods for additional analyses (e.g., subgroup analyses) {20b}

Not applicable.

### Methods in analysis to handle protocol non-adherence and any statistical methods in analysis to handle protocol non-adherence and any statistical methods to handle missing data {20c}

We perform statistical analysis on complete case.

### Plans to give access to the full protocol, participant-level data, and statistical code {31c}

All data sharing will be conducted in accordance with the regulatory requirements.

## Oversight and monitoring

### Composition of the coordinating center and trial steering committee {5d}

In order to control the quality of the clinical trial, the whole process of the trial will be conducted under the supervision of a qualified clinical trial expert in Shanghai Municipal Hospital of Traditional Chinese Medicine. The Clinical Research Center for Drugs of Shanghai University of Traditional Chinese Medicine will conduct the data monitoring. When problems occur in the trial, the center has the right to make the final decision to terminate the trial if necessary. Any changes will be notified in writing to all participants in the trial after approval by the ethics committee. The principle investigator will be fully responsible for conducting the trial and will make any final decisions.

### Adverse event reporting and harms {22}

We will record any adverse events such as bleeding, hematomas, fainting, bruising, ecchymoma, and possible infection.

### Frequency and plans for auditing trial conduct {23}

We will audit every 3 months; any modification that may have an impact on the study and potential benefit to patients or affect patient safety, including changes of the study objective, study design, patient population, sample size, study procedure, or serious adverse events, will be reported to the Committee. This will be decided by jointly with the monitoring committee, the Clinical Research Center of Drugs, and approved by the Ethics Committee.

### Plans for communicating important protocol amendments to relevant parties (e.g., trial participants, ethical committees) {25}

When the trial protocol is modified during the trial, we will conduct a discussion group composed of statisticians, acupuncturists, gastroenterologists, etc. After collective discussion, the next step of the trial plan will be drawn up and the clinical plan updated on the clinical trial registration website.

### Dissemination plans {31a}

The publication of the outcomes of this study will provide baseline data. The outcomes may be presented at conferences, symposiums, university classes, etc., if applicable.

## Discussion

Acupuncture therapy has been effectively used in clinical practice for relieving symptoms caused by clinical surgery. For example, Wang et al. [15] ADDIN show that acupuncture may reduce the side effect of vomiting during gastroscopy by adjusting the function of vegetative nerves, regulating gastrointestinal tract function, and reducing the concentration of blood 5-HT. Taras I U [16] found that auricular acupuncture (AA) is a promising alternative treatment for situational anxiety. Andrzejowski JC [17] found that acupuncture at the EX-HN3 point reduces preoperative anxiety levels in patients awaiting neurosurgery. However, these existing literatures have inevitable deficits: differing acupuncture intervention method such as using ear acupuncture or intra-dermal needles and a lack of a uniform standard for the setting of intervention time. Some papers have reported that when applied before gastroscopy acupuncture has no apparent differences compared to sham acupuncture [18, 19]. So, in this trial, we used the study by Liu et al. [20], which has been widely used in clinical practice as a successful implementation of sham acupuncture, to rule out the placebo effect of acupuncture in a rigorous way. Studies have shown that superficial acupuncture in non-acupoints method has the advantages of providing a good masking effect and being not easily perceived by the patient and has a higher feasibility of operation. One clinical trial of acupuncture treatment for pain found that the superficial acupuncture at non-acupoints method is an effective way to control for placebo [21]. By designing this RCT, we aim to contribute better evidence for the efficacy of electroacupuncture in reducing discomfort during gastroscopy through an improved design and methods.

For patients, surgical procedures performed in hospitals are a strong stressor and can lead to an anxiety response. Excessive anxiety can affect immune mechanisms through the release of corticosteroids and may be associated with abnormal hemodynamics as a consequence of endocrine changes and activation of the central nervous system [22, 23]. A high level of preoperative anxiety will also reduce patients’ satisfaction with the procedure and increase the risk of postoperative nausea and vomiting [24, 25]. So, in this trial, we will focus on preoperative anxiety. The STAI-S6 and APAIS are reliable means of assessing patient anxiety [26, 27]. By using these questionnaires, we can quickly and accurately assess patients’ anxiety level in a few minutes.

Previous findings have shown that gastroscopy may bring a series of complications to patients with hypertension, such as myocardial infarction, cardiac arrest, and other complications [28]. Some research has shown that in patients older than 45 years, the risk of cardiovascular disease doubles with an increase in systolic blood pressure of 20 mmHg or a diastolic blood pressure increase of 10 mmHg [29, 30]. So, in our study, we will monitor BP before, during, and after gastroscopy, then analyze the correlation between DP and the primary outcome of VAS score to determine whether EA can reduce stress placed on the heart, and thus benefit elderly people with cardiovascular related diseases who need gastroscopy.

There are several limitations in this study. First of all, we did not limit any comorbidities that patients may have. Patients who meet our inclusion criteria and need upper gastrointestinal endoscopy according to the assessment of a gastroenterologist can be included in this trial. Some comorbidities like pharyngitis might increase sensitivity and discomfort when the gastroscope passes through the pharynx. Therefore, we cannot precisely determine the impact of comorbid diseases on the level of anxiety during gastroscopy. Secondly, based on the previous pilot research, the sample size of this RCT include 60 patients, which is still a small-scale study involving a small sample, but the data obtained in this study will support the sample size calculation of future multi-center, large-scale clinical trials. We hope, in the future, the data will have guiding significance for subsequent clinical trials related to acupuncture intervention in gastroscopy. Finally, it is inevitable for the acupuncturist to know the grouping of patients. We hope that this limitation will be offset by the fact that the acupuncturist does not participate in the evaluation of the questionnaire and that the patients are subjected to rigorous blinding practices.

We aim to design a standard and rigorous RCT to reduce discomfort during gastroscopy by acupuncture treatment. We believe acupuncture will increase patient compliance and ease the gastroscopy-related burden on public health services. With positive results, our research will serve as a new standard of care for patients hoping to forego systemic sedation during gastroscopy procedures.

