### Trial design {8}

This RCT is a single-site randomized placebo-controlled trial. It will be implemented in Shanghai Municipal Hospital of Traditional Chinese Medicine. All eligible patients will be randomly assigned to the electroacupuncture group (EA) or the sham electroacupuncture (SEA) group in a 1:1 allocation ratio. All patients must sign the informed consent form before they are enrolled in the trial. The research process flow chart is detailed in Fig. 1. In this trial, the Consolidated Standards of Reporting Trials (CONSORT) [13] and acupuncture reporting guidelines, Standards for Reporting Interventions in Clinical Trials of Acupuncture (STRICTA) [14], will be followed.

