#### Secondary outcomes

The patient’s level of discomfort at 7 days post-procedure by using VAS. The four VAS including nausea and vomiting, throat discomfort, bucking, and agitation will present separately as secondary outcomes at 30 min and 7 days post-procedure.Cardiac-respiratory assessment

All patients’ pulse oxygen saturation (SpO2), heart rate (HR), and blood pressure (BP) measurements will be recorded prior to, during, and post-procedure. Then, each patient’s “double product” (DP) will be calculated at each point of the procedure, based on the systolic blood pressure (SBP) and heart rate (SBP×HR). DP is a useful prognostic tool for patients with poor cardiac function during exercise and rest, reflecting myocardial oxygen consumption and cardiac output during treadmill testing. A value of DP greater than 15,000 indicates cardiovascular stress. It is accepted that changes in cardiac output from baseline (preoperative) will reflect the level of stress experienced by patients undergoing the gastroscopy.
Anxiety level

A six-item short form of the State-Trait Anxiety Inventory (STAI-S6) and Amsterdam Pre-operative Anxiety and Information Scale (APAIS) will assess the degree of preoperative anxiety, postoperative anxiety, and 7 days post-procedure. These questionnaires are quick and simple for participants to complete, which is advantageous in time-restricted studies.
Preference in a future endoscopy

The questionnaire will ask patients whether they have undergone gastroscopy before, and then ask, “Do you have interest in taking acupuncture treatment for to avoid the post-operative discomfort before next gastroscopy?”
Safety assessment

Before participants sign the informed consent form, they will be informed that acupuncture clinical trials may have potential adverse events such as bleeding, hematomas, fainting, bruising, ecchymoma, and possible infection. All details of the adverse event will be recorded by the patients and doctors. Adverse events (AE) are rated as 1 (mild), 2 (moderate), or 3 (severe or medically significant). All details of AEs will be recorded in the case report form (CRF). At the end of the trial, we will analyze the impact of all events.
Blinding success assessment

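### The Discussion would judge whether EA lowers cardiac stress from a DP–VAS correlation, which contains no treatment contrast; the conclusion should rest on the between-arm comparison of DP.

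*Protocol article*

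**What the plan says.** - **Discussion.** After describing cardiovascular risk during gastroscopy, the article says the trial will record BP before, during and after the procedure and "then analyze the correlation between DP and the primary outcome of VAS score to determine whether EA can reduce stress placed on the heart". It goes on to a possible benefit for elderly patients with cardiovascular disease.
- **Secondary outcomes, cardiac-respiratory assessment.** DP is defined here: "each patient’s “double product” (DP) will be calculated at each point of the procedure, based on the systolic blood pressure (SBP) and heart rate (SBP×HR". The section adds that "A value of DP greater than 15,000 indicates cardiovascular stress" and that "changes in cardiac output from baseline (preoperative) will reflect the level of stress experienced by patients undergoing the gastroscopy".
- **Statistical methods {20a}.** A general rule covers primary and secondary outcomes: "measurement data between the two groups will be analyzed with the" t-test and rank-sum test. DP, a time point and a correlation method are not named.
- **Section {20b}, additional analyses.** The entry is "Not applicable".
- **Table 4.** HR, BP and SpO2 are marked before, during and 30 min after the operation. There is no mark at baseline or before the intervention.

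**The concern.** The Discussion sentence names an analysis, the causal question it is meant to settle, and the clinical claim that would follow. The analysis does not fit the question. DP during endoscopy and VAS at 30 min are both measured after randomisation, and their correlation across patients is an observational association. Treatment group does not appear in it. Whether EA lowers DP is a question about the difference in DP between the randomised arms.

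If the sentence were followed, a cardiac benefit could be claimed from nothing more than the fact that patients who gag and struggle have a faster pulse and higher pressure. A real reduction in DP could also be overlooked because it was not accompanied by a strong link to VAS.

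**Working it through.** The plan states no figure for this analysis, so there is none to reproduce. The check asks how often each analysis would be significant under stated scenarios.

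**Inputs from the protocol (Sample size section)**
- Pilot VAS: EA 4.8 (SD 1.76), SEA 6.3 (SD 1.53). Difference 1.5.
- Pooled SD = √[(1.76² + 1.53²)/2] = 1.649.
- Standardised VAS effect a = 1.5/1.649 = 0.91.
- 50 evaluable patients at 1:1, hence 25 per arm; two-sided 5%.

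**Assumptions (not in the protocol)**
- b: reduction in DP under EA, in SD units.
- r: correlation of DP and VAS within each arm.
- Bivariate normal data.

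**What the pooled correlation measures.** With equal arms, the expected correlation over all patients is

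ρ = (r + ab/4) / √[(1 + a²/4)(1 + b²/4)].

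The within-arm link r enters directly. The EA effect on DP enters only through the product ab/4 and the variance term. Two examples, with a²/4 = 0.207:
- No DP effect, r = 0.4: ρ = 0.4/√1.207 = 0.36, although b = 0.
- DP reduction of 0.9 SD, r = 0: ab/4 = 0.91 × 0.9/4 = 0.205 and b²/4 = 0.2025, so ρ = 0.205/√(1.207 × 1.2025) = 0.17, although EA has a large effect on DP.

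**Simulated rejection rates** (25 per arm, at least 5,000 trials per scenario; pooled Pearson test of DP against VAS, and between-arm t-test of DP)

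| EA effect on DP | Within-arm r | Correlation significant | Between-arm DP test significant |
|---|---|---|---|
| none | 0 | about 5% | about 5% |
| none | 0.2 | about 24% | about 5% |
| none | 0.4 | about 75% | about 5% |
| none | 0.5 | about 92% | about 5% |
| lowers by 0.9 SD | 0 | about 21% | about 87% |
| lowers by 0.9 SD | 0.4 | about 97% | about 87% |
| raises by 0.8 SD | 0.8 | about 98% (mean r +0.51) | about 80%, in the harmful direction |

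The correlation column follows mainly r. The between-arm column follows the EA effect on DP and does not depend on r. The last row is an extreme case, but it shows that a positive, significant correlation is compatible even with harm.

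**What the between-arm test can detect.** With 25 per arm, a two-sided 5% t-test detects 0.81 SD with 80% power and 0.94 SD with 90% power. With 30 per arm the figures are 0.74 and 0.85 SD. Without a DP SD in the protocol these cannot be put in mmHg × beats per minute.

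**The case against.** The strongest reply is that the right comparison is already planned. DP is listed under secondary outcomes, and {20a} compares measurement data between the groups. That stands. A reader might infer from the Discussion that no between-arm comparison of DP is intended, and the document does not support that inference. The time point and any adjustment may properly be left to an analysis plan that is not shown. What the general rule does not do is correct the Discussion sentence, which ties the cardiac conclusion to the correlation alone.

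Two other strong readings also fail. One is that the correlation contradicts {20b}. That item gives subgroup analyses as its example, so an exploratory correlation missing from it is at most a small listing gap. The other is that the correlation undermines the randomisation. It makes no use of the randomisation, but it leaves the randomised comparison of DP intact.

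It is also fair to say that the percentages depend on assumed values. With no DP effect, the correlation is significant in about 24% of trials at r = 0.2 and about 92% at r = 0.5. With a 0.9 SD reduction in DP and r = 0, the figure falls from about 21% to about 5% only if EA also has no effect on VAS, which is not what the trial is planned around. The direction of the argument does not depend on any one of these values.

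Lastly, the sentence stands in the Discussion. But it is written as a plan for this study, and it is the only place where an analysis is attached to the cardiac question.

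**Conclusion.** The stated rule of inference is wrong as written: a DP–VAS correlation cannot determine whether EA reduces cardiac load. Under the assumed scenarios, with 25 per arm and the pilot VAS effect, it is significant in about 24% to 92% of trials when EA does nothing to DP (r of 0.2 to 0.5), against about 5% for the between-arm test. It is significant in about 21% against 87% when EA lowers DP by 0.9 SD and r is zero. These figures illustrate the mismatch and do not predict this trial.

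The scope is limited: one sentence about a secondary outcome, with a suitable between-arm comparison already implied elsewhere and no effect on the primary analysis. It is worth correcting because the sentence leads directly to a claim of clinical benefit.

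**What to change.** - Reword the Discussion sentence so that the conclusion about EA and cardiac stress rests on the between-arm difference in DP during endoscopy, with a 95% CI, under the general rule in {20a}.
- Keep the DP–VAS correlation as descriptive, and state that it supports no inference about an EA effect. Listing it under "Methods for additional analyses (e.g., subgroup analyses) {20b}" would be tidy.
- Do not rely on adjustment for a pre-acupuncture DP. Table 4 schedules no HR or BP before the intervention, and the preoperative value is taken after the 30-min treatment. It may already carry part of any EA effect, so change from that value should not be presented as change from an untreated baseline.

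The cost is a change of wording. HR and BP are already scheduled during endoscopy, so no new measurement and no change to the sample size is needed.

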### Trial status

We started recruiting participants in February 2021 and the recruitment is expected to end late 2021.

## Abbreviations

VAS: Visual analogue scales
STAI-S6: The 6-item short form of the State-Trait Anxiety Inventory
APAIS: Amsterdam Pre-Operative Anxiety and Information Scale
SpO2: Pulse oxygen saturation
HR: Heart rate
BP: Blood pressure
STRICTA: Standards for Reporting Interventions in Clinical Trials of Acupuncture
